### Recruitment {15}

#### Clinician Enrollment

The principal investigator will present the study overview in either department meetings or in one-on-one conversations with eligible clinicians. If the principal investigator is not available, then the study coordinator or another member of the study team will reach out to the clinician to see if they are interested in participating. If the clinician is interested, then a member of the study team will review and have them complete the consent.

#### Patient Enrollment

The study coordinator will scan upcoming appointments for enrolled clinicians in the EHR for potential eligible patients. After screening, if a patient appears to be eligible, they will contact the clinician to confirm. Once confirmed the study coordinator may reach out to the patient by one of the following methods: 1) Meet with patients as they are roomed to discuss the study and review the consent process, 2) Contact the patient by phone to see if they would be interested in participating, or 3) Contact the patient through the patient portal.

The study coordinator will consent both clinician and patient for video/or audio recording of the encounters. Any adult who accompanies the patient into the exam room for the appointment will be orally consented to being video/or audio recorded.

Patient Consent: Patients’ consent may be completed in person or online depending on the means of recruitment. A copy of the consent form is attached as Additional file 5.

### Allocation: sequence generation {16a}

#### Patient allocation:

Eligible patients will be allocated at 1:1 ratio into either usual care alone or NSCLC Choice. Block randomization will be completed using random block sizes stratified by clinician. The randomization will be carried out by a statistician using the REDCap platform (18, 19)

### Allocation Concealment mechanism {16b}

The allocation sequence will be concealed using the REDCap platform (18, 19) and is not accessible to be viewed or modified.

### Allocation Implementation {16c}

Initially, patients will be enrolled by study coordinators who are unaware of the study arm to which the patient will be assigned. Once a patient is enrolled and has provided written or electronic consent, the study coordinator will record the data in REDCap. Following this, participants will be randomized into one of the two arms of the study based on the randomization sequence.

### Assignment of interventions: Blinding

#### Who will be blinded {17a}

The clinician will not be blinded to the arm assignment due to the nature of the intervention. The patient is made aware of an educational intervention that may be used in the encounter, staying blind to the hypotheses of the trial. Study personnel collecting outcome data from the recordings and the study analyst will not be blind to the trial arm.

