### Outcomes {12}

Patient outcomes, Primary Endpoints:

To assess the primary endpoint of SDM process quality, two measures will be collected.

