#### OPTION12:

an observer scale applied to recorded encounters which assesses the degree of effort the clinician made to involve patients in SDM. The scale consists of 12 items scored from 0, no effort to 4, exemplary effort. The 12 items are summed and converted to a 100-point scale. Initially, a sample of 20% of the recordings will be assessed by two or more reviewers. Agreement will be assessed by Lin’s concordance index, where any value over 0.8 will be considered concordant. Once the agreement is reached, other videos will be reviewed. If concordance does not occur within the first 20% encounters, the two reviewers will assess cases of difference and review an additional 10 cases to test for agreement. Recordings scored by both reviewers will be averaged (15).

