Data from the medical records of all enrolled patients will be abstracted to capture demographic and clinical information, covering the period from before enrollment to 6 weeks after enrollment. Data collected on patients will include variables such as Eastern Cooperative Oncology- performance status(ECOG-PS), previous treatments for NSCLC, mutations, smoking history, marital status, education, race/ethnicity, and annual income (20, 21).

In addition to data captured through surveys and EHR data, we will also capture data through video or audio recording of the clinical encounter. For in-person encounters, the study coordinator will set up the portable digital video camera at the start of a visit where both the patient and clinician have consented. The camera will be aimed at the clinician’s desk, away from the physical examination table. The clinician and the patient will be instructed on how to occlude the lens, direct the camera to a wall or turn off the camera at any time they feel this is appropriate. After the visit the study coordinator will retrieve the recording device. For virtual visits the study coordinator will join the virtual visit to record the meeting and administer the survey. After the encounter, study coordinators will transfer the video file to a secure server for analysis, deleting the recording from the device after server confirmed backup. These recordings will be used to assess SDM (OPTION) as well as contamination and fidelity intended use (OSIM).

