### Data management {19}

The study will use the most current versions of all documents and forms, and the study team will follow the established study schedule. Data will be entered into the REDCap system, a HIPAA-compliant, secure platform that ensures validated data entry, edit checks, and logs of all data modifications. The statistical team will have access to the data at any time and can download it into statistical software for analysis. Data will be reviewed monthly by the statistical team to verify its accuracy and completeness. All data, documents, and analysis results will be stored within the health system, which is password-protected and backed up nightly.

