### Data monitoring: interim analysis {21b}

No interim analysis is planned.

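### OPTION12 raters and the study analyst are left unblinded without a stated reason; full rater masking is not possible, but allocation could be withheld from both

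*Protocol article*

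**What the plan says.** All places are in the protocol article.

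- **Raters and analyst.** Who will be blinded {17a}: "Study personnel collecting outcome data from the recordings and the study analyst will not be blind to the trial arm". No reason is attached.
- **Clinician.** The same section does give a reason here: "The clinician will not be blinded to the arm assignment due to the nature of the intervention".
- **Status of OPTION12.** Outcomes {12}: "To assess the primary endpoint of SDM process quality, two measures will be collected". These are SDM-Q-9, reported by patients, and OPTION12, described as "an observer scale applied to recorded encounters which assesses the degree of effort the clinician made to involve patients in SDM". OPTION12 has 12 items scored 0 to 4, rescaled to 100 points.
- **Rater quality control.** "Initially, a sample of 20% of the recordings will be assessed by two or more reviewers". Agreement is judged by Lin's concordance, with values over 0.8 accepted.
- **Second use of the recordings.** Plans for assessment and collection of outcomes {18a} has the same recordings serve both OPTION and the OSIM coding of contamination and fidelity.
- **Data access.** Data management {19}: "The statistical team will have access to the data at any time and can download it into statistical software for analysis". A monthly review by that team checks accuracy and completeness.
- **Interim looks.** Data monitoring {21b}: "No interim analysis is planned".

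**The concern.** OPTION12 asks a rater to judge how hard a clinician tried to involve the patient. A rater who knows the arm may score tool encounters more generously, and that error falls directly on the comparison by assigned arm. A positive OPTION12 result would then be hard to separate from rater expectation.

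The analyst's case differs. The design does not require the analyst to know which arm is which while the data are checked and the analysis program is written. The article gives no reason for the unblinding, and the statistical team can download the accumulating data at any time. Some choices are not fixed in the article, such as the covariates of the adjusted models and the priority between the two primary measures. An analysis plan that is not shown may settle them. If it does not, they could be settled by someone who can see the arms.

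**Working it through.** **1. The plan's own figure, and whether it is touched.** Sample size estimation {14} gives SD 20, a 12-point difference, 50 per group, ICC 0.01 and two-sided alpha 0.05. With DE = 1 + (m − 1) × 0.01 and power = Φ(12 / (20 × √(2 × DE / 50)) − 1.96):

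- m = 5: DE = 1.04, power = Φ(2.942 − 1.96) = 83.7% (82.9% with the t distribution; stated 82%).
- m = 10: DE = 1.09, power = Φ(2.873 − 1.96) = 82.0% (81.1% with t; stated 80%).

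The figures agree within 2 points. They concern SDM-Q-9, which raters do not score, so this point leaves the sample size alone.

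**2. Whether concordance protects OPTION12.** Lin's coefficient is 2·cov / (var₁ + var₂ + (mean₁ − mean₂)²). Suppose both raters add the same b points to tool-arm recordings. Their difference on each recording does not change. With 1:1 allocation and no true effect, the covariance and both variances each rise by b² × 0.5 × 0.5 = b²/4. Take equal rater means and variances, a coefficient of 0.80 before the bias, and b = 5, so that b²/4 = 6.25:

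- SD 10: (80 + 6.25) / (100 + 6.25) = 0.812.
- SD 20: (320 + 6.25) / (400 + 6.25) = 0.803.

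A shared bias therefore raises concordance slightly. The check can find raters who differ, not raters who are wrong together.

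**3. What a shared shift could do (illustration only).** The article gives no OPTION12 SD and no size of bias, so both are assumed here. With 50 scored recordings per arm, SE = SD × √(2/50) = 0.2 × SD. With no true effect, the two-sided rejection rate is 1 − Φ(1.96 − b/SE) + Φ(−1.96 − b/SE), ignoring clustering:

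| Average shift b | SD 10 (SE 2) | SD 15 (SE 3) | SD 20 (SE 4) |
|---|---|---|---|
| 2 points | 17% | 10% | 8% |
| 3 points | 32% | 17% | 12% |
| 5 points | 71% | 38% | 24% |

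The nominal rate is 5%.

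**4. How much of that is avoidable.** Only recordings that do not themselves reveal the arm can gain from withholding allocation. If these are a fraction f of each arm, and knowing the arm moves their scores by δ, the avoidable shift is f × δ. A 5-point effect of knowing the arm would have to act in 2/5 = 40% of recordings to move the contrast by 2 points. The article does not allow f to be estimated, but it shows that f is not zero:

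- Clinicians may decide against using the tool with an enrolled patient (Mode of use {11d}).
- Recordings may be audio (Patient Enrollment; {18a}).
- The lens may be covered, or the camera turned away or switched off ({18a}).
- Tool use in usual care is foreseen and monitored (Usual care encounters).

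**5. Whether coded arms would mask the analyst.** Not alone. Tool use is itself coded from the recordings for fidelity and contamination, and those variables would show which code is the tool arm. They have to be withheld together with the arm field. Allocation: sequence generation {16a} has a statistician carry out the randomization, and the team description {5d} lists one statistician role, responsible for analysis. If these are the same person, recoding masks little.

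**The case against.** The strongest reply is that the article is being candid. In the tool arm the aid is normally in view, and usual-care clinicians are told not to use it, so raters will often know the arm whatever is done. Recordings already carry a code number without identities (Confidentiality {27}), and the article does not say that raters are handed the allocation. The order of OPTION12 and OSIM scoring is a detail that a coding manual might hold. All of this stands, and it limits the point to partial masking. It does not explain why {17a} leaves raters unblinded for recordings that would not reveal the arm, or why it includes the analyst.

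Three stronger readings are tempting and are not supported.

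- **That every analysis choice is exposed.** The statistical methods section {20a, 20c} fixes intention to treat, cluster-adjusted t and chi-square tests, hierarchical models with clinician random effects, and no imputation. Alpha is set in {14}, and no additional analyses are planned {20b}.
- **That continuous access means informal interim comparisons.** The stated purpose of the monthly review is data quality, and no interim analysis is planned. Retraining is triggered by the quality of delivery seen on recordings, and adding centres by accrual; neither is triggered by outcome results. Access by an unblinded team is a weakness of safeguards, not evidence of looks.
- **That the bias is as large as the effect sought.** A half-point leniency on every item gives 0.5 × 12 = 6 of 48 raw points, or 12.5 of 100. The half-point is assumed, and the 12-point target belongs to SDM-Q-9, a different instrument.

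**Conclusion.** The concern holds in a limited form. The article states, without a reason, that OPTION12 raters and the analyst are unblinded. One measure of the primary endpoint is thus open to an expectation bias that its only stated check cannot detect. The bias can be reduced for raters but not removed. For the analyst, masking up to program lock is feasible, unless the same person set up the randomization.

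The size is unknown. The 8% to 71% range in the table rests on assumed SDs of 10 to 20 and assumed average shifts of 2 to 5 points. It describes total rater bias, of which only the part from recordings that do not show the arm can be avoided. SDM-Q-9 and the power calculation are unaffected by rater bias. The article does not contradict itself here; this is a stated design choice that should be improved at little cost.

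**What to change.** 1. **Who will be blinded {17a}.** State that raters have no access to the allocation record. State also that OPTION12 is scored for each recording before, and separately from, its OSIM fidelity and contamination coding.
2. **Data management {19}.** Run the monthly accuracy and completeness checks on data without the arm field and without the tool-use and OSIM variables.
3. **Analyst.** Supply data with arms coded A and B, also without those variables, until the database and the primary analysis program are locked. If the statistician who sets up randomization is also the analyst, say that this masking is limited.
4. **Reporting.** State that rater masking is partial because the tool may be seen or heard, and give this as a limitation of the OPTION12 result.

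The cost is a change to access rights and to the order of coding. Sample size and patient procedures do not change. The downside is that masking stays incomplete, and that a second person may be needed to prepare the coded file if one statistician holds both roles.

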#### Procedure for Unblinding if needed {17b}

This study is not blinded; therefore, no unblinding procedures are applicable.

### Data Collection and Management

#### Plans for assessment and collection of outcomes {18a}:

Patients who are approached by study staff and agree to participate will be recorded in REDCap.

Potential patients who are found to be ineligible or those who decline participation will be documented in a recruitment tracking log, including reasons for ineligibility or decline, along with the patient’s age, sex, and race/ethnicity.

Self-reported data from patients and clinicians will be collected at multiple timepoints throughout the study (Table 1). At enrollment, clinicians will complete a demographic survey that includes questions on age, gender, race, ethnicity, and years in practice. After the index encounter, both patients and clinicians will complete a survey at the clinic, facilitated by the study coordinator or site-appointed staff. For virtual encounters, the survey will be provided electronically for completion. The post-encounter survey for patients will collect patient demographics, SDMQ9, knowledge, decision made, satisfaction, DCS, health literacy(20), and numeracy (21). If the encounter is in-person and the patient requests a return envelope, one will be provided to mail the completed survey back. If the survey is not returned within 10 days, a reminder will be sent with a new copy of the survey and a return envelope. A courtesy reminder call will be made within 5 days after the mailing. For virtual encounters, the study coordinator will join the session at the end to present the survey and assist the patient in completing the online form. If the patient cannot stay on the call, a paper survey will be mailed following the same procedure as for in-person encounters. Every effort will be made to complete the survey immediately after the encounter in the clinic for the most accurate data collection.

Patients will also receive a follow-up survey to be completed 2 weeks after enrollment, with the mode of completion based on patient preference (e.g., mail, online via email, or a portal message). Incomplete surveys will be conducted according to the same follow-up process described above.

Data from the medical records of all enrolled patients will be abstracted to capture demographic and clinical information, covering the period from before enrollment to 6 weeks after enrollment. Data collected on patients will include variables such as Eastern Cooperative Oncology- performance status(ECOG-PS), previous treatments for NSCLC, mutations, smoking history, marital status, education, race/ethnicity, and annual income (20, 21).

In addition to data captured through surveys and EHR data, we will also capture data through video or audio recording of the clinical encounter. For in-person encounters, the study coordinator will set up the portable digital video camera at the start of a visit where both the patient and clinician have consented. The camera will be aimed at the clinician’s desk, away from the physical examination table. The clinician and the patient will be instructed on how to occlude the lens, direct the camera to a wall or turn off the camera at any time they feel this is appropriate. After the visit the study coordinator will retrieve the recording device. For virtual visits the study coordinator will join the virtual visit to record the meeting and administer the survey. After the encounter, study coordinators will transfer the video file to a secure server for analysis, deleting the recording from the device after server confirmed backup. These recordings will be used to assess SDM (OPTION) as well as contamination and fidelity intended use (OSIM).

### Plans to promote participant retention and complete follow-up {18b}

Participants have the right to withdraw from the study at any time, for any reason. An expected dropout rate of approximately is <1% anticipated based on previous studies. To minimize dropouts, patients will receive phone or electronic reminders to complete the questionnaires.

### Data management {19}

The study will use the most current versions of all documents and forms, and the study team will follow the established study schedule. Data will be entered into the REDCap system, a HIPAA-compliant, secure platform that ensures validated data entry, edit checks, and logs of all data modifications. The statistical team will have access to the data at any time and can download it into statistical software for analysis. Data will be reviewed monthly by the statistical team to verify its accuracy and completeness. All data, documents, and analysis results will be stored within the health system, which is password-protected and backed up nightly.

### Confidentiality {27}

In this study, participant privacy will be safeguarded by ensuring that no names are used on any research data (including field notes, transcriptions of conference calls, meeting recordings, audio and video recordings of interviews, and transcripts). Participants will be assigned a unique study code number for identification. The link between the code number and participant identity will be stored in a secure, firewalled spreadsheet on a research server, accessible only to study investigators and study staff, all of whom have human subjects research certification. This spreadsheet will be deleted once all participant follow-up is complete. A do-not-call list will be maintained for individuals who decline participation to prevent multiple contact attempts, as patients may have several appointments at participating clinics during the study. All research materials will be stored securely on a server or in locked file cabinets, and all materials will be destroyed seven years after the study’s completion.

Digital recordings of clinical encounters will be immediately uploaded to the research team’s secure server and deleted from portable devices after overnight back-up of servers. The video and audio files will be identified using a code number that does not include the name of the clinician, support staff, or patient or reference to their medical record number or date of birth. The research data is only accessible with password protected and logged access.

### Plans for collection, laboratory evaluation and storage of biological specimens for genetic or molecular analysis in this trial/future use {33}

Not applicable, as no biological specimens are collected in this study.

## Statistical Methods

### Statistical methods for primary and secondary outcomes {20a} and {20c}

The study will be analyzed according to the *intention to treat principle (ITT)*, including all patients enrolled in the study and analyzed in the arm to which they were assigned, regardless of which intervention they received. Descriptive statistics will be conducted with means and standard deviations for continuous variables and counts and frequencies for categorical variables. We will use cluster (cluster at clinician level) adjusted t-test and chi-square test for comparisons between interventions and hierarchical generalized linear models (HGLMs) with random main effects specified at the clinician level when adjusting by more than arm. If clustering is not present, then the results will reduce to a model that assumes independence and reflects findings appropriately. Missing data will not be imputed for the analysis. Rates of missing data will be reported in the findings.

### Statistics: additional analyses {20b}

No planned additional analysis.

### Plans to give full access to the full protocol, participant level data and statistical code {31c}

The full study protocol will be available and published. Participant-level data will not be accessible due to privacy and confidentiality concerns, and a statistical analysis code will not be provided.

### Oversight and monitoring

#### Composition of the coordinating center and trial steering committee {5d}

This is a single center study conducted and managed by the oncology department within an academic medical center. The responsibilities within the research team are as follows:

Principal investigator/ Lead investigator: Responsible for overseeing study design, preparation of protocol including revisions, and identification and recruitment of clinicians.

##### Study coordinator:

Handles participant consent, data collection, clinical trials registration and communication with the IRB.

##### Statistician:

Responsible for data analysis.

The study team will meet weekly. No trial steering committee or stakeholder/public involvement group (nor any other committee) will be involved.

